### Design

The study is performed as a cluster-randomized controlled trial over the course of 3 years. The randomization clusters are represented by public daycare centers in the city of Frankfurt am Main, Germany that were assessed before being randomized. Figure 1 summarizes the study design.

**Figure 1 F1:**
[figure not shown]
Study design.

### Outcome

The primary measure of outcome, the Manchester Child Attachment Story Task (MCAST) [42], seems to be a promising approach to evaluate results beyond the well established cognitive measures and questionnaires. Attachment representations are found to be crucial moderators for child development [43], highlighting the importance of parenting practices for children with low-SES status [4,43,44]. Therefore, the intervention response is defined as the change from children’s insecure attachment representation to a more secure one. Within the insecure attachment representations, intervention response is also defined as the change towards a more structured attachment representation (that is, statistically significant change in the disorganization score and the narrative coherence score, Likert scale, range 1 to 9).

Second outcome measures include the German adaptation of HAWIVA [41], the C-TRF [33,34], the SDQ [35,36] from the teacher’s and parent’s perspective, and the PERIK [37,38].

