### Objectives and hypothesis

The purpose of the trial is to investigate the differential efficacy of the two intervention programs in a high-risk population. The first hypothesis assumes that the program Early Steps, which individually addresses the child’s particular needs, is more effective than the standardized curriculum Faustlos in preventing aggressiveness, hyperactivity and anxiety. Secondly, we hypothesize that the more restricted approach of Faustlos might better meet the teachers’ demand for structure in some daycare centers depending on the institutional setting. Therefore, we are also interested in investigating the effectiveness of the prevention program in relation to its actual fit to the needs of the institution. Thirdly, we hypothesize that a subgroup of children in the program Early Steps will exhibit a change in their insecure attachment representation towards one that is more structured or secure.

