### Power analysis

The sample calculation and power analysis is based on α = 0.05 at a power of 0.80, using the pre/post differences of the mentioned FPS. We expect at least an effect size of *d* = 0.5. Further, if we used a RCT study design for analysis of variances, the minimum sample size would be *n* = 63 per treatment. In contrast, we applied a CRCT design with the daycare centers as given clusters. (Note: each daycare center represents one cluster.) We used a formula introduced by Eldridge *et al*. [45], providing a conservative estimate of sample size requirements for trials using cluster-level analyses weighted by cluster size.

$$n*=\left\{1+\left[\left(1+\mathrm{CV}2\right)\times m–1\right]\times \mathrm{ICC}\right\}\times n$$

The formula for the corrected sample size *n** consists of the coefficient of variation *CV* for trials with unequal cluster sizes (that means with unequal sizes of daycare centers) and the intra class correlation coefficient *ICC* within the clusters and the mean cluster size *m*. Using again the findings of the Frankfurt Prevention Study, the estimated coefficient of variation is *CV* = 0.467 and the estimated intra class correlation coefficient (based on the pre/post differences including the *CV*) *ICC* = 0.0465. We expect a mean cluster size *m* = 20 or at least *m* = 17 children. The corrected sample size for the first scenario would be *n** = 131.44 (if *m* = 20) divided by 20 = 6.57; in the second scenario *n**=120.73 (if *m* = 17) divided by 17 *n** = 7.10. For both scenarios, seven clusters, respectively seven daycare centers per treatment, should be selected.

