### Planned analyses for the primary outcome

#### Primary outcome: MCAST attachment representation

Data will be analyzed with respect to the intention of treatment. We will describe all baseline characteristics at the individual as well as at the cluster level. Moreover, we will assess the characteristics of any cluster and if the children drop out. Relevant characteristics will be added if applicable as covariates to the models. Children’s attachment representations are measured on MCAST’s overall attachment classification (secure vs insecure-ambivalent vs insecure-avoidant vs insecure-disorganized attachment representation) and on MCAST’s disorganization and narrative coherence scores. As the main analysis involves changes in MCAST disorganization and narrative coherence scores from the baseline and the endpoint in the intervention versus the control group, an analysis of covariance is applied with repeated measures and linear regression with autocorrelated data (compound symmetric covariance structure models). Changes in the overall attachment classifications are calculated by tests for frequency distributions and procedures of survival analysis (Cox, regression, log-rank tests). All procedures take the CRCT design into account. Therefore, variances of the sample mean will be corrected using the factor *n**/*n* (as described above).

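### Response is defined by statistical significance, the MCAST primary outcome is not one variable, and the first hypothesis rests on secondary measures

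*Protocol article*

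**What the plan says.** **Response.** The Outcome section of the protocol article names the MCAST as the primary measure and gives two definitions of response. One is a move from an insecure to a more secure representation. The other applies within the insecure representations and is a more structured representation, spelled out as "statistically significant change in the disorganization score and the narrative coherence score, Likert scale, range 1 to 9". No number of scale points is given.

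**Analysis.** The section Primary outcome: MCAST attachment representation lists the four-way classification, the disorganization score and the narrative coherence score. It states that "the main analysis involves changes in MCAST disorganization and narrative coherence scores from the baseline and the endpoint", compared between intervention and control. Changes in classification are handled separately, by frequency tests and survival methods.

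**Sample size.** The Power analysis section is "based on α = 0.05 at a power of 0.80" and adds: "We expect at least an effect size of *d* = 0.5". Before clustering, "the minimum sample size would be *n* = 63 per treatment". The effect size is not tied to a named MCAST result.

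**Hypotheses.** In Objectives and hypothesis, the first is that Early Steps "is more effective than the standardized curriculum Faustlos in preventing aggressiveness, hyperactivity and anxiety". The third is that "a subgroup of children in the program Early Steps will exhibit a change in their insecure attachment representation" towards a more structured or secure one. The Outcome section classes the behavior questionnaires (C-TRF, SDQ, PERIK) as secondary.

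**The concern.** Three statements in the article do not fit together.

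1. **The response definition cannot be applied.** Whether a change is significant depends on the number of children and the spread of their scores. The same mean change can be significant in a large sample and not in a small one. It therefore gives no rule for classing a child as a responder.
2. **The primary outcome is an instrument, not a variable.** Two scores share the main analysis and a classification stands beside them. The article does not say which result decides the trial, or whether one or both scores must succeed. The sample size assumes a single test.
3. **The hypotheses and the primary outcome are ranked in opposite orders.** The first hypothesis is about behavior, which is secondary. The primary construct, attachment, appears only in the third hypothesis, for a subgroup of one arm and with no comparator.

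What is at stake is the meaning of a positive result. A favorable finding on one MCAST result could be presented as success. Alternatively, the MCAST could show nothing while the first hypothesis is claimed from secondary scales.

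**Working it through.** **Inputs from the article (Power analysis).** α = 0.05, power 0.80, d = 0.5, CV = 0.467, ICC = 0.0465, m = 20 or 17, seven centers per arm. Sidedness is not stated.

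**Step 1: reproduce the stated sample size.** For two means, two-sided:

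n = 2(1.960 + 0.842)² / 0.5² = 62.8, so 63 per arm. A one-sided test would need only about 50, so 63 matches one two-sided test at 0.05.

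Design effect = 1 + [(1 + CV²)m − 1] × ICC, with 1 + CV² = 1.2181:
- m = 20: 1 + 23.362 × 0.0465 = 2.0863; × 63 = 131.44; / 20 = 6.57 centers.
- m = 17: 1 + 19.708 × 0.0465 = 1.9164; × 63 = 120.73; / 17 = 7.10 centers.

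All stated figures reproduce. They cover one test.

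**Step 2: count the candidate results.** The narrowest reading is the two scores of the main analysis. The wider reading adds the classification, which sits under the same primary heading. Each result is counted once, although several methods are listed for the classification.

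**Step 3: family-wise error if any one result suffices at two-sided 0.05.** If independent: 1 − 0.95² = 9.75% for two and 1 − 0.95³ = 14.3% for three. The correlations below are assumptions (simulated normal test statistics, 1,000,000 draws):

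| Assumed correlation | Two scores | Three results |
|---|---|---|
| 0 | 9.75% | 14.3% |
| 0.3 | 9.5% | 13.6% |
| 0.5 | 9.1% | 12.5% |
| 0.7 | 8.4% | 10.9% |
| 0.9 | 7.0% | 8.4% |

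**Step 4: if both scores must succeed.** The error stays at or below 0.05. If each score has power 0.80, joint power is 0.80 × 0.80 = 0.64 when the tests are independent, and reaches 0.80 only when they are perfectly correlated.

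**Step 5: what a split of alpha would cost.** Effective n per arm with seven centers is 140 / 2.0863 = 67.1 (m = 20) or 119 / 1.9164 = 62.1 (m = 17). Power = Φ(0.5 × √(n_eff / 2) − z), normal approximation, d = 0.5 for every result:

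| Alpha per result | m = 20 | m = 17 |
|---|---|---|
| 0.05 (one primary) | 82.5% | 79.6% |
| 0.025 (two results) | 74.4% | 70.7% |
| 0.0167 (three results) | 69.2% | 65.2% |

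The last two rows are Bonferroni figures. Holm is never less powerful, so they are floors for Holm. To keep 80% at the Bonferroni level, the need before clustering is 77 per arm for two results (77 × 2.0863 / 20 = 8.03 and 77 × 1.9164 / 17 = 8.68, so 9 centers per arm). For three results it is 84 (8.76 and 9.47, so 9 to 10 centers).

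**The case against.** **The article does rank the results in part.** It calls the two-score analysis the main one. That stands: the narrow reading has two candidates and an error of at most 9.75%. The wording also joins the scores with *and*, which may mean that both must change; then there is no inflation. No sentence says that each result is tested at 0.05.

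**Multiplicity rules are often left to the SAP.** That also stands, and the lack of an adjustment rule is not the point here. The point is that the article names an instrument as primary, sets two scores side by side as its main analysis, and sizes the trial for one test.

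**Significant change could mean reliable change in an individual child.** That would be usable, but the article gives no reliability figure or threshold. Supplying one amounts to stating a number of scale points, which is the fix below.

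**Two stronger readings are not supported.** A reader might infer that the trial could succeed on change within Early Steps alone. The planned main analysis compares intervention with control, and the stated purpose is differential efficacy; the loose wording is confined to the response definition and the third hypothesis. A reader might also infer that the endpoint could be t2 or t3. The abstract speaks of measurement before and after 2 years of intervention, and Table 2 labels t2 as post study and t3 as follow-up, so t2 is the natural reading.

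**Conclusion.** The point holds in three parts. The response definition cannot be used as written. The primary outcome is not reduced to one variable or one success rule, although the sample size assumes one two-sided test at 0.05. The first hypothesis rests on measures that the article classes as secondary, while attachment comes third and without a comparator.

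The size depends on the success rule, which the article does not settle. If any one result suffices at 0.05, the error is about 7% to 9.75% for two scores and about 8% to 14.3% for three, over assumed correlations from 0.9 down to 0. If both scores must succeed, the cost is power: anywhere from 0.64 (independent tests) up to 0.80 (perfect correlation) when each score has 0.80. The 14.3% is therefore an upper figure for one reading (three results, none negatively correlated), not the error rate of the plan.

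**What to change.** 1. Delete the reference to statistically significant change. Define response by attachment category or by a fixed number of scale points, and compare it between arms.
2. Designate one MCAST score as the single primary result: the baseline-adjusted difference between arms at t2. This keeps the stated 63 per arm before clustering and seven centers per arm. Which score is the sponsor's choice; the article gives no basis for preferring either. The alternative is Holm across the MCAST results, with the power restated.
3. Restate the attachment hypothesis as Early Steps versus Faustlos.
4. Reconcile the order of the hypotheses with the primary outcome by labelling the behavior hypothesis as secondary.

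**Cost.** Only wording changes. With one primary score, the remaining MCAST results become secondary. With Holm, power per result falls, to no less than about 71% to 74% for two results or 65% to 69% for three under the assumptions above, unless centers are added. In either case the first-listed hypothesis no longer carries a confirmatory claim. That is a real loss, but it follows from having made attachment primary. Placing behavior behind a chain of attachment tests is not recommended: the article offers no basis for such an order, and behavior could then be confirmed only after every attachment test had succeeded.

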### Power analysis

The sample calculation and power analysis is based on α = 0.05 at a power of 0.80, using the pre/post differences of the mentioned FPS. We expect at least an effect size of *d* = 0.5. Further, if we used a RCT study design for analysis of variances, the minimum sample size would be *n* = 63 per treatment. In contrast, we applied a CRCT design with the daycare centers as given clusters. (Note: each daycare center represents one cluster.) We used a formula introduced by Eldridge *et al*. [45], providing a conservative estimate of sample size requirements for trials using cluster-level analyses weighted by cluster size.

$$n*=\left\{1+\left[\left(1+\mathrm{CV}2\right)\times m–1\right]\times \mathrm{ICC}\right\}\times n$$

The formula for the corrected sample size *n** consists of the coefficient of variation *CV* for trials with unequal cluster sizes (that means with unequal sizes of daycare centers) and the intra class correlation coefficient *ICC* within the clusters and the mean cluster size *m*. Using again the findings of the Frankfurt Prevention Study, the estimated coefficient of variation is *CV* = 0.467 and the estimated intra class correlation coefficient (based on the pre/post differences including the *CV*) *ICC* = 0.0465. We expect a mean cluster size *m* = 20 or at least *m* = 17 children. The corrected sample size for the first scenario would be *n** = 131.44 (if *m* = 20) divided by 20 = 6.57; in the second scenario *n**=120.73 (if *m* = 17) divided by 17 *n** = 7.10. For both scenarios, seven clusters, respectively seven daycare centers per treatment, should be selected.

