**Methods/Design:**

Preschoolers in 14 daycare centers in Frankfurt, Germany, participate in a cluster randomized controlled trial (CRCT). The daycare centers were randomly chosen from a representative baseline survey of all Frankfurt’s daycare centers carried out in 2003 (*n* = 5,300) with the following stratifying factors: children’s aggressiveness, hyperactivity, anxiety and socioeconomic status. Additionally, the geographic identification of socioeconomically deprived neighborhoods regarding low-income children was taken from the Frankfurt Municipality Statistics. Children’s attachment classification and children’s aggressiveness, hyperactivity, anxiety and social competence are measured as outcome criteria before and after 2 years of intervention. The programs in the study aim to reach a high-risk population. Therefore, the combination of a random sampling of daycare centers out of a representative baseline survey in all daycare centers in Frankfurt and the application of official data on the local distribution of low-income children are unique features offered by the EVA study design. Data on preschooler’s attachment representations are collected in socioeconomically deprived neighborhoods for the first time.

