### Representativeness of the sample and sample selection (at cluster level)

In 2003, the Sigmund Freud Institute carried out a baseline survey of all Frankfurt daycare centers (114 centers with approximately 5,300 children, aged 3 to 4). Children’s aggressiveness, hyperactivity and anxiety were measured using the teachers’ ‘observation questionnaire for preschool children’ [46]. Additionally, the SES of all daycare centers was assessed, operationalized as the family’s dependency on financial support by the Frankfurt Municipality that paid the monthly fee for the daycare center indicating low SES. These data were stratified by aggressiveness, hyperactivity, anxiety and SES and resulted in the division of 114 daycare centers into 10 clusters (see Table 1). EVA daycare centers were randomly chosen out of the clusters’ groups with low SES. (Note: here we are considering clusters on a higher level, each cluster contains several daycare centers).

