## Discussion

The EVA study is carried out in the Center for Research on Individual Development and Adaptive Education of Children at Risk (IDeA) with financial support from the State of Hessen, Germany. One major aim of the IDeA Center is to improve the social integration and positive development of children at risk. Previous studies showed evidence of accumulation of psychosocial problems in socioeconomically deprived neighborhoods [5-8,47] and found that parenting characteristics moderate the association between SES and children’s cognitive and academic achievements [4]. Therefore, the EVA study investigates children at risk in socioeconomically deprived neighborhoods where their families face multiple challenges. Moreover, findings of attachment research influenced the EVA study design. Hence, attachment representations as crucial moderators for child development [43] highlight the importance of a ‘good enough’ early child–parent relationship experience. A secure attachment relationship between infant and caregiver is associated with optimal infant development and positive social development, including higher levels of social competence, more advanced emotional understanding and higher cognitive and language skills [48,49]. In contrast, children with an insecure-disorganized attachment representation show the highest risk later, demonstrating behavior problems that include clinical levels of externalizing and/or aggressive symptoms, hostility in the classroom as well as poor academic achievement [50-52]. This knowledge motivated us to implement an instrument in the EVA study design to classify children’s attachment representations using the MCAST. We expect to find a high- risk population regarding children’s attachment representations and to detect a high percentage of insecurely attached children. Several program modules of Early Steps (such as psychotherapy for children and their parents within the daycare center and the individual mentoring by student teachers during the transition from kindergarten to primary school) particularly address children at risk, respectively children with insecure-disorganized attachment representations. Especially for these children, we expect an improvement of their attachment representation after the individual treatment in the Early Steps group.

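### The stated 0.80 power rests on earlier behaviour data that the article never links to MCAST, so it is unsupported (not shown to be too low) for the primary outcome

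*Protocol article*

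**What the plan says.** The Power analysis section of the protocol article opens: "The sample calculation and power analysis is based on α = 0.05 at a power of 0.80". The same sentence names the basis, "at a power of 0.80, using the pre/post differences of the mentioned FPS", and the section continues: "We expect at least an effect size of *d* = 0.5". No outcome or scale is attached to that d. For an individually randomized trial, "the minimum sample size would be *n* = 63 per treatment". This is inflated for clustering with CV = 0.467 and ICC = 0.0465, both attributed to the FPS, the ICC specifically to its pre/post differences. The result is seven daycare centers per arm. MCAST is not mentioned in the section.

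The Outcome section is explicit: "The primary measure of outcome, the Manchester Child Attachment Story Task (MCAST") is primary, and the teacher and parent questionnaires are secondary. Under Planned analyses for the primary outcome, the main analysis is change in the MCAST disorganization and narrative coherence scores. Variances there are to be corrected by n*/n, with a reference back to the power calculation.

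On the FPS, the Background reports effects on aggressiveness, anxiety and hyperactivity, for a prevention group against a control group. The section on representativeness says that in the 2003 survey "aggressiveness, hyperactivity and anxiety were measured using the teachers" own observation questionnaire. On attachment, the Discussion says of the research on insecure attachment: "This knowledge motivated us to implement an instrument in the EVA study design to classify" attachment representations with the MCAST. The abstract says that data on "attachment representations are collected in socioeconomically deprived neighborhoods for the first time".

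**The concern.** Power belongs to a particular outcome, because the standardized effect and the ICC are both properties of the variable analysed. A teacher's rating of aggressive behaviour and a psychologist's assessment of a doll-play narrative differ in construct and in informant. Teacher ratings can cluster within a center for reasons that need not apply to independent assessors. There is no reason given why the ICC of one should equal the ICC of the other, or why the expected d should carry over.

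Two things are at stake. First, a null MCAST result could be taken as coming from a trial with 80% power on its primary outcome, which the article has not shown. Second, read as written, the n*/n correction carries the borrowed ICC from planning into the primary test, where a wrong value changes the standard error.

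**Working it through.** **Inputs, all from the Power analysis section:** α = 0.05 (two-sided reproduces the printed n), power 0.80, d = 0.5, CV = 0.467, ICC = 0.0465, mean center size m = 20 or 17, k = 7 centers per arm.

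**1. Reproducing the plan.**
- Before clustering: n = 2(1.96 + 0.8416)² / 0.5² = 62.8, so 63 per arm.
- Design effect: DE = 1 + [(1 + CV²)m − 1] × ICC, with 1 + 0.467² = 1.2181.
- m = 20: DE = 1 + (24.362 − 1) × 0.0465 = 2.0863; n* = 63 × 2.0863 = 131.44; 131.44/20 = 6.57 centers.
- m = 17: DE = 1 + (20.708 − 1) × 0.0465 = 1.9164; n* = 63 × 1.9164 = 120.73; 120.73/17 = 7.10 centers.

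All printed figures match.

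**2. Power with seven centers per arm.** Power = Φ(d / √(2·DE/(7m)) − 1.96).
- m = 20: √(2 × 2.0863/140) = 0.1726; 0.5/0.1726 − 1.96 = 0.936; power 0.825.
- m = 17: √(2 × 1.9164/119) = 0.1795; 0.5/0.1795 − 1.96 = 0.826; power 0.796.

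**3. Which inputs depend on the outcome.** CV is variation in center size, so it does not depend on what is measured and is not at issue. The ICC and d do depend on it.

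**4. Range for MCAST.** The article gives no MCAST effect, SD or ICC, so the ICC values 0.02 and 0.10 and the d values below 0.5 are assumptions. Minimum detectable d at 80% power = 2.8016 × √(2·DE/(7m)).

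| ICC | DE (m = 20/17) | Power at d = 0.5 | Minimum detectable d |
|---|---|---|---|
| 0.02 (assumed) | 1.467/1.394 | 0.93/0.90 | 0.41/0.43 |
| 0.0465 (FPS) | 2.086/1.916 | 0.825/0.796 | 0.48/0.50 |
| 0.10 (assumed) | 3.336/2.971 | 0.63/0.61 | 0.61/0.63 |

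With the ICC held at 0.0465, d = 0.4 gives 0.64/0.61 and d = 0.3 gives 0.41/0.39. The plan's normal approximation is kept throughout, so that only the inputs vary.

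**5. Effect on the primary test.** If variances are inflated with the FPS-based DE when the true one differs, the test statistic is off by √(DE true/DE used), and type I error = 2[1 − Φ(1.96 × √(DE used/DE true))]. At m = 20:
- True ICC 0.10: √(2.0863/3.3362) = 0.791; 1.96 × 0.791 = 1.55; type I error about 0.12.
- True ICC 0.02: √(2.0863/1.4672) = 1.192; 1.96 × 1.192 = 2.34; type I error about 0.02.

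These two are illustrations on assumed ICCs.

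**The case against.** The best defence is that planning from the same institute's earlier study in Frankfurt daycare centers is ordinary practice when nothing better exists, and that d = 0.5 is offered as an expectation, not as an FPS estimate. A standardized d also has no units, so a difference in measurement scale alone does not invalidate it. That the FPS held no attachment data is inferred: the Background summarizes FPS results without listing every measure, and the abstract's remark about first collection concerns deprived neighborhoods only. The article may condense a fuller justification.

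Much of this stands. The FPS origin of d follows from the preceding sentence and is not stated outright. The absence of MCAST from the FPS is likely, not proved. It does not rescue the 0.80, however. The article prints a complete calculation and names its source, and that source is not linked to the outcome declared primary. The ICC is stated to come from FPS pre/post differences.

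Two stronger readings are tempting, and the article supports neither. A reader might infer that the trial is underpowered for MCAST; the assumed ranges fall on both sides of 0.80, so this is not shown. A reader might also infer that the 0.80 holds for the first hypothesis, on behaviour. But EVA measures behaviour with the C-TRF, SDQ and PERIK, whereas the only earlier instrument named is the teachers' observation questionnaire. The FPS compared prevention with control, whereas EVA compares two active programs, one of which contains the other. The article also does not say which FPS outcome gave the ICC.

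**Conclusion.** The concern holds in a limited form. The 0.80 is computed correctly from its inputs, but the article does not support it as the power of the primary MCAST analysis. It is not shown to be too low, nor is it established for the behaviour outcomes.

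Over an assumed MCAST ICC of 0.02 to 0.10, power at d = 0.5 runs from 0.93/0.90 down to 0.63/0.61, and the minimum detectable d from 0.41/0.43 up to 0.61/0.63. The conclusion rests on two readings: that d = 0.5 was taken from the FPS, and that the FPS had no MCAST data. The first could be wrong without changing the position on the ICC. If the FPS did hold MCAST data, the article would only need to say so and give the values.

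The reuse of n*/n in the primary analysis is the part with consequences beyond wording, because it makes the validity of the test depend on the borrowed ICC.

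**What to change.** **Power analysis section.** State that d and the ICC come from FPS behaviour differences, prevention versus control, and that no MCAST-specific values were available (or give them, if they were). Do not relabel the 0.80 as established power for the first hypothesis. For the MCAST disorganization and narrative coherence scores, replace the single figure with conditional power or minimum detectable d at seven centers per arm, over a stated range of ICC and d, such as the table above.

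**Planned analyses for the primary outcome.** Base the cluster correction of the MCAST analysis on the ICC estimated from the MCAST data instead of the FPS-based n*/n. Report that ICC together with the confidence interval of the arm difference, so that a null result is judged by its precision.

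**Cost.** One reworded paragraph, one small table and one changed sentence in the analysis section. No centers or children are added. The stated power becomes conditional and may look less favourable, and an ICC estimated from 14 centers will itself be imprecise.
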